Orthokeratology (OrthoK) is an application of a rigid gas permeable contact lens with a base curve significantly flatter than the corneal curvature to temporarily reduce myopia. OrthoK is used during sleeping time. Clinical evidence point at an effect of up to 40% reduction in myopia progression. Soft contact lenses are also used to control myopia. There are several designs of SCLs available, with the most recent one (MiSight from Coopervision, a dual focus soft contact lens) being effective in up to 60% reduction of myopia and being the first soft contact lenses receiving an FDA approval for controlling myopia progression. Atropine drops for controlling myopia are available in various doses. Low dose Atropine is a common myopia control treatment all over the world including Israel and is available at the Health maintenance organizations in Israel with a deductible, although it's not part of the medical services basket. The low dose Atropine drops are considered to be an effective treatment with no side effects. Some of the spectacle lenses for myopic control have not been clinically evaluated for myopia control at all, some were evaluated and found to be ineffective, and some have declared clinically proven effect of up to 50-60% reduction in myopia progression. A new clinically effective design of spectacle lens is MyoSmart from HOYA (DIMS, defocus incorporated multiple segments). MyoSmart's design comprises a 9mm central optical zone and a 33mm annular zone with multiple 1mm segments having a relative positive power of +3.50 D, thus making the lens appear to have multiple ‘dimples’ in the periphery, although close inspection is required to see them. MyoSmart was clinically tested and found to be effective in up to 60% reduction of myopia compared to a regular single vision lens^5^. Another new clinically effective design of spectacle lens is Stellest by Essilor. Its mechanism is similar to the one of MyoSmart^6^ and its two years results show an effect of 55% in slowing down the progression of myopia^7^. A third spectacle lens is MyoVision by Zeiss. Its mechanism is also based on the defocus concept. An older version of MyoVision was clinically tested and was found to have no significant effect on the progression of myopia^8^. The latest version of MyoVision has not yet been clinically evaluated. Taking into account all available myopia control treatments, a cosmetically appealing, high compliance, low-cost and clinically effective spectacle lens for myopia control is expected to be a well-accepted low-risk and non-invasive treatment.

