- Previously been treated with any myopia control treatments (Orthokeratology, myopia control spectacle/contact lenses, multifocal lenses, bifocal lenses, atropine)

| Trial Plan |
| --- |

Screening visit **(VISIT 1)**

- Enrollment criteria verification
- Signing informed consent
- Baseline documentation of medical history, parental and siblings myopia, indoor and outdoor activities profile and socioeconomic profile
- Lensmeter measurements of patient's spectacles
- Performing baseline measurements including best corrected VA, objective & subjective refraction under cycloplegia, PR under cycloplegia*, slit lamp examination, functional tests: cover test, titmus test, worth four dot test, axial length** and pupil size measurements
- Frame selection and frame measurements
- Lens order completion and sending to Shamir Optical Industries for manufacturing

Randomization Procedures (following VISIT 1)

Randomization procedures should be performed by the trial coordinator following visit 1. The patient will then be allocated to the test or control group.

Manufacturing Procedures (following VISIT 1)

The manufacturing technician will take care of the manufacturing processes according to the lens type (ib test or control) and the mounting on the frame. The test spectacles will then be sent to the site for delivery.

Delivery visit **(VISIT 2)** performed ~10 days after screening visit

- Trial spectacles delivery
- Subjective questionnaire while wearing the trial spectacles
- Best corrected far and near VA (with the trial spectacles)
- Confrontation visual field test with the trial spectacles
- Giving instructions about wearing the trial spectacles
- Documenting adverse events if relevant

Follow-up visit performed 6 months (±1 week) after the previous visit **(VISITS 3,4,5,6)**

- Documentation of any change medical history since last visit
- Subjective questionnaire regarding the wearing period with the trial spectacles (feedback performing follow-up measurements including best corrected far and near VA, objective & subjective refraction under cycloplegia, PR under cycloplegia*, slit lamp examination, functional tests: cover test, titmus test, worth four dot test, axial length and pupil size measurements

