- If the subjective refraction will find a SE (Sphere Equivalent) change from last refraction of at least -0.50D, a new lens order should be made for new lenses, and a delivery visit should be set in order to deliver the new test spectacles. The procedures mentioned above in the delivery visit (visit 2) should then be performed.
- Documenting adverse events if relevant

Additional unscheduled visits

- May be scheduled as needed if special needs occur
- Procedures will be defined by the investigator
- Documenting adverse events if relevant

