**Total duration of trial per patient: 24 months.**

**A unique measurement performed using a designated device that measured the refractive error in the peripheral retina and. Duration of measurement – 15 minutes.*

**Axial Length is measured using TOMEY optical biometer OA-2000 (partial coherence interferometry). The measurement is performed without any contact with the patient's eye.

| Ethical Issues |
| --- |

This trial will be conducted according to the applicable local regulations and the GCP. All essential documents will be reviewed and approved by the ethics committee prior to the beginning of the trial. Any amendments of these documents will be reviewed and approved by the ethics committee prior to implantation in the trial.

Informed Consent

The investigator will give the child and their parent/legal guardian a full explanation about the trial and will answer all their question regarding participating in the trial.

The investigator will explain that the child will be able to withdraw from the trial at any stage for any reason.

The child's parent/legal guardian will sign the informed consent form and will receive a signed copy of it.

Data confidentiality

All identification details about the children participating in the trial will be held by the investigator in a secured log file kept at the trial site.

Access to the identification details will not be allowed to any unauthorized party and will not be disclosed in any report/document relating to the trial.

Terminating the participation in the trial

These are the cases in which an early termination of the participation in the trial may occur:

1. Should the myopia progression of the patient will be more than 1.00 D after 1 year or other significant refractive changes (such as more than 0.5[D] cylinder) - the investigator will recommend the patient to discontinue the participation in the trial and to consider using other myopia control treatments such as low dose Atropine drops.
2. Should the far/near VA with the trial spectacles will be less than the best corrected VA of the patient, the investigator will consider recommending the patient to discontinue the participation in the trial.

| Risk Evaluation/Adverse Events |
| --- |

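### Children who meet the cylinder or acuity ground are advised to leave the trial altogether, and no outcome measurement is described after they go

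*Protocol*

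**What the plan says.** The Protocol, under Ethical Issues (Terminating the participation in the trial), lists two numbered cases for early termination.

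- **Refractive change.** Besides progression above 1.00 D after a year, the first case covers other changes: "other significant refractive changes (such as more than 0.5[D] cylinder) - the investigator will recommend the patient to discontinue the participation in the trial". This must mean a change in cylinder, because the inclusion criteria already admit astigmatism up to 1.50 D. The same sentence advises the child to "consider using other myopia control treatments such as low dose Atropine drops". The background section says of that treatment: "The low dose Atropine drops are considered to be an effective treatment with no side effects".
- **Acuity.** The second case reads "Should the far/near VA with the trial spectacles will be less than the best corrected VA of the patient", and then "the investigator will consider recommending the patient to discontinue the participation in the trial". This is softer than the first: the investigator only has to consider giving the advice.

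Under Data Analysis (Outcome measures analysis), change from baseline in cycloplegic refraction (primary) and axial length (secondary) is calculated at 6, 12, 18 and 24 months. It is analysed by t-test and by linear mixed models. The Trial Plan gives 24 months as the duration per patient. Nowhere does the protocol describe refraction or axial length measurement, or recording of other treatment, in a child who has left on either ground.

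**The concern.** Stopping a treatment and leaving a trial are different events, and this section merges them. A child may have good reason to stop the trial lenses, yet measuring that child at 12, 18 and 24 months is still possible and useful. If the child leaves, those values are never taken, and no later choice of analysis can supply them.

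Two features make this more than ordinary dropout. The cylinder ground is itself a refractive change, in a trial whose primary outcome is refraction, so those who leave may differ in outcome from those who stay. These children are also pointed towards a treatment that the protocol itself regards as effective, so it matters whether and when they start it. At stake are the completeness of the 18- and 24-month comparisons in particular, and the ability to judge whether the children who left differ from those who remained.

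**Working it through.** **1. The plan's own figure.** Inputs from Sample size calculation: difference 0.18 D per year, SD 0.35 D. Two-sided 5% and 80% power are assumed, as the section states neither.

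n per group = 2 × (1.96 + 0.8416)² × 0.35² / 0.18² = 2 × 7.849 × 0.1225 / 0.0324 = 59.35, rounded up to 60. Total: 120 × 1.05 + 10 = 136. Both figures reproduce.

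The 10 extra children are for high annual progression. Cylinder and acuity exits therefore share the 5% allowance, 126 − 120 = 6 children, with every other cause of dropout.

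**2. Outcome values lost per child.** Planned after baseline: 4 visits × 2 outcomes = 8.

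| Last visit attended | Values lost |
| --- | --- |
| Visit 2, delivery (acuity ground) | 4 × 2 = 8 |
| Visit 3, 6 months | 3 × 2 = 6 |
| Visit 4, 12 months | 2 × 2 = 4 |
| Visit 5, 18 months | 1 × 2 = 2 |
| Visit 6, 24 months | 0 |

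The visit at which the ground is found still yields its own values. Exit at or after Visit 4 therefore costs no 12-month value. For the cylinder ground, the Visit 3 row applies only if that ground operates before one year.

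**3. Link to the primary outcome.** The Data Analysis section defines SE = SPH + CYL/2. With sphere unchanged, a 0.50 D change in cylinder moves SE by 0.25 D, and a 0.75 D change moves it by 0.375 D. Sphere may move as well, so the ground is related to the outcome without determining it.

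**4. What cannot be computed.** The protocol gives no rate for either ground and nothing on differences between arms. The ranges below rest wholly on assumed values.

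- *Power.* After the planned losses, (136 × 0.95 − 10) / 2 = 59.6 per arm remain, giving power 80.2%. Further losses of 5%, 10%, 15% and 20% leave 56.6, 53.6, 50.7 and 47.7 per arm, with power 78.1%, 75.9%, 73.5% and 70.9%. The design figures are annual, so this describes a comparison at 12 months of children measured then, and only exits before that measurement count.
- *Bias.* Annual progression was simulated as normal with means 0.60 D (control) and 0.42 D (test), SD 0.35 D, and exit correlated with progression at r = 0.3 to 0.6. The true difference is 0.18 D.

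| Exit rate, control / test | Observed difference (r = 0.3 to 0.6) |
| --- | --- |
| Equal (5% / 5% or 10% / 10%) | 0.18 D |
| 5% / 10% | 0.189 to 0.198 D |
| 5% / 15% | 0.197 to 0.214 D |
| 10% / 5% | 0.171 to 0.162 D |

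The sign depends on which arm loses more children, which the protocol does not let a reader predict.

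**The case against.** The strongest case is that little may be lost. Exit is only advised, and on the acuity ground the advice is itself discretionary. The qualifier of one year in the first case may also govern the cylinder change; if so, that ground costs no 12-month value. The 5% allowance is not limited by cause and may absorb these exits. The mixed models use the visits before exit, including the one at which the change was found. Missing measurement after exit is also not peculiar to these grounds: it applies equally to the progression ground in the same sentence.

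Most of this stands as a limit on size. None of it supplies the missing follow-up. The models must extrapolate for children who have gone, and a t-test at a given visit can use only those measured there. Nor can a statistical analysis plan, which may exist but is not shown, settle the matter: whether children keep attending is trial conduct, fixed in the protocol.

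A reader might go further and infer that new lenses and a retest should be required before anyone is advised to leave. The document does not support that.

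- The cylinder ground is met by the eye's measured refraction, which new spectacles do not change. The accompanying advice on other treatment makes it read as a rescue rule.
- The stated lens-order trigger is "SE (Sphere Equivalent) change from last refraction of at least -0.50D, a new lens order should be made". A cylinder-only change above 0.50 D and below 1.00 D would miss it, but that window is nearly empty. With 0.75 D of minus cylinder, only 0.50 − 0.375 = 0.125 D of myopic sphere change triggers an order.
- The two thresholds may not share a reference point, since none is given for the cylinder change.
- The discretionary wording of the acuity ground already permits re-correction first. So do unscheduled visits, for which "Procedures will be defined by the investigator".

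**Conclusion.** The point holds as a gap in follow-up: on two stated grounds children are steered out of the trial rather than off the lens, and nothing describes measuring them afterwards. Its size is certain only per child: four of eight values for exit after Visit 4, and up to all eight for an acuity exit at delivery. The missing values may be informative because the cylinder ground shares a component with the primary outcome.

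A reader might infer that the trial is biased in favour of the test lens, or underpowered. Neither follows: exit rates, their split by arm and their relation to progression are not given, and the power and bias figures above only illustrate assumed values. This is a low-cost improvement worth making, not an error that invalidates the design. Confidence is medium, mainly because the timing of the cylinder ground is ambiguous and the number of exits is unknown.

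**What to change.** Amend the section on terminating participation as follows.

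1. Meeting the cylinder or acuity ground leads to advice (for acuity, at the investigator's discretion as now) to stop trial lens wear and consider other treatment, not to leave the trial.
2. The scheduled cycloplegic refraction and axial length visits continue to 24 months where the family agrees, and the child is analysed in the randomised arm.
3. The ground met, the date lens wear stopped, and any other myopia treatment with its start date are recorded.
4. An analysis using data only up to the stop date is reported beside the randomised-arm analysis.

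The amendment should also say whether the one-year qualifier applies to the cylinder ground. The same wording can cover the progression ground. The family's right to withdraw and the investigator's discretion to stop a child for safety stay as they are.

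The cost is a short amendment with the ethics committee review that the protocol already requires, a few extra data fields, and visits that are already planned. The downside is that values taken after the stop date may reflect stopping the lens or starting atropine, which is why item 4 is needed.

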This will be a controlled, randomized, double-masked trial. The Test group will wear the myopia control spectacle lens and the Control group will wear the single vision spectacle lens.

Primary outcome measure:

The mean change from baseline in objective cycloplegic refractive error in each of the groups (Test and Control)

Secondary outcome measure:

The mean change from baseline in axial length in each of the groups (Test and Control)

| Trial Product |
| --- |

Test lenses: Myopia control design spectacle lens, material: 1.6 High-Index plastic.

Control lenses: Single Vision design spectacle lens, material: 1.6 High-Index plastic.

Both test and control lenses will be designed and manufacture by Shamir Optical Industries Ltd.

Both test and control lenses will be mounted on regular frames.

Test lens

The test lens is manufactured in a standard FreeForm technology (exactly like a standard progressive addition lens which is similar in terms of the graduall power profile induced in both lens). It does not demand any special manufacturing processes.

The test lens should be worn exactly like a standard spectacle lens and it should be worn through all day hours. The fitting of the test lens is done exactly like the fitting of the control lens, according to the manufacturer instructions.

Product Labeling and Accountability

The clinical trial coordinator, who is in charge of the randomization procedures, will be also in charge of labeling the test spectacles per each patient prior to sending the spectacles to the site. The investigator will hold a dispensing log in which there will be a documentation of the product:

- on receival from the manufacturer
- on dispensing to the patient
- on receiving back from the patient if applicable

| Enrollment |
| --- |

**136** participants will be enrolled in this trial (including an estimated dropout rate of ~5%), 68 participants will be randomly allocated to the Test group and 68 participants will be randomly allocated to the Control group.

Sample size calculation

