The annual myopia progression rate (in objective refraction) in children in Israel is estimated as 0.6D. The effect estimated is 30% which is a change of 0.18D between the annual myopia progression rate at the test group and the control group. Taking into account a standard deviation of the progression rate of 0.35D (as reported in the scientific literature in western countries), the sample size of each group (test and control) should include 60 children.

Taking into account a drop out rate of 5% and also a certain amount of drop outs during the trial due to high annual myopia progression (as mentioned in the section about terminating the participation in the trial) for which we added 10 more patients, the overall calculated sample size is 136.

Distribution of ages within the sample:

The age range for inclusion in the trial is 6 to 12 years old and the children will be enrolled into two aged groups: young children and older childern. In order to create an equal amount of children within each age group the enrollment will be as follows:

- Young Children: Age ≥6, <9.5: 68 patients
- Older Children: Age ≥9.5, <13: 68 patients

Randomization

Randomization function should be applied separately per each of the two age groups, so that eventually each group will contain an equal number of Test lens wearers and the Control lens wearers.

Randomization function will be applied per each age group by the clinical trial coordinator who will keep the randomization list in a confidential file and will not disclose it to other trial staff members (except for the manufacturing technician at Shamir Optical Industries) until the trial close up unless required in specific cases of trial withdrawals by the investigator.

Inclusion Criteria

- Informed consent form signed and fully comprehended by the parent/legal representative of the child
- Age from 6 to 12 years old
- Both male and female
- Spherical Equivalent refractive error (cycloplegic objective) of -0.50D to -5.00D
- Astigmatism not higher than -1.50D
- Corrected Visual Acuity of not less than 6/7.5 or 20/25
- Willing to wear the trial spectacles for the defined period according the protocol plan

Exclusion Criteria

- Current participation in another clinical trial
- Any general health or ocular health pathology that could affect the treatment
- Allergy or intolerance to cycloplegic eye drops (*name should be stated here*)
- Strabismus
- Amblyopia
- History of ocular injury or ocular surgery

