The optical design of the test lens, with the gradual positive peripheral power, induce a certain amount of aberrations in the peripheral areas of the lens. These aberrations were designed such that a good level of compliance will be achieved so that the children will be able to wear the lens.

Adverse events are unlikely to occur, yet it should be mentioned that a child should not wear this lens in case of one/more of the following exist:

- Feeling significant amount of discomfort while wearing the lens such that the safety of the child might be at risk.
- Vestibular disorders

The children participating in the trial will be free to contact the investigator at any time during the wearing period in order to report any unexpected events that might occur. The investigator will decide based on the report whether the child should be excluded from continuing the trial.

Furthermore, it should be noted that a parallel clinical trial is being conducted these days in AIER hospital in China, managed and supervised by Brien Holden Vision Institution (Australia). The trial is similar to our trial, with the same trial product, on a group of 140 children with the same enrollment criteria, including similar trial procedures and trial plan. The trial started at November 2020, and as for now most of the children has worn the test spectacles for a few months with no adverse events reported.

| Data Management |
| --- |

Database

An electronic data base will be held and maintained, into which all the source data will be electronically transferred from the measuring devices, or if not possible, will be typed in and source data (printouts or location of data) will be kept in the patient's file. At any case, all source data (printouts or location of data) should be kept in the patient's file.

The electronic data base will be backed up on a daily basis

Access to data:

The investigator will be able to allow access to data to the Sponsor (without identification data) as per request.

The investigator will be able to allow access to data to the Monitoring staff according to the monitoring plan that will be defined.

| Data Analysis |
| --- |

Data analysis will be performed by a third party. The trial raw data (without the identification data) will be transferred to the third party following the completion of each follow up visit. The third party will then perform the data analysis and produce a report to the sponsor.

Outcome measures analysis:

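### Vestibular disorders are a stated reason not to wear the test lens, but no exclusion criterion names them, although screening is the last check before masked randomisation

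*Protocol*

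**What the plan says.** The Risk Evaluation/Adverse Events section of the protocol states that "a child should not wear this lens in case of one/more of the following exist". Two items follow: discomfort during wear large enough to put the child's safety at risk, and "Vestibular disorders". The second carries no qualifier.

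The Exclusion Criteria do not name vestibular disorders. The closest entry is "Any general health or ocular health pathology that could affect the treatment".

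The screening visit (Visit 1) includes "Enrollment criteria verification" and "Baseline documentation of medical history, parental and siblings myopia, indoor and outdoor activities profile and socioeconomic profile". It lists no vestibular question or test.

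On allocation, "Randomization procedures should be performed by the trial coordinator following visit 1". The Trial Design section says "This will be a controlled, randomized, double-masked trial". Under Randomization, the coordinator keeps the list confidential and "will not disclose it to other trial staff members", apart from the manufacturing technician. Earlier disclosure is foreseen only for particular withdrawal cases.

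**The concern.** The protocol gives a pre-existing medical condition as a reason not to wear the investigational lens, yet the eligibility list does not carry it over. A site working from the exclusion list could enrol a child whom the risk section says should not wear the test lens, and the child could then be allocated to it.

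Timing and masking make the entry list the right place for this. The contraindication concerns the test lens only. Before randomisation it can be applied to every child alike. After randomisation a masked investigator who learns of the condition has two choices: stop a child who may be wearing ordinary single-vision lenses, or ask for the allocation to be disclosed.

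What is at stake is the safety of children aged 6 to 12 and consistency between two sections of the protocol. No effect on sample size, endpoint, analysis or balance between the arms is claimed.

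**Working it through.** The protocol gives no figure on this point, so the check is mainly a comparison of its sections.

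**1. Is the condition named at entry?** The seven exclusion criteria are:

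| # | Exclusion criterion (paraphrased) | Names vestibular disorders? |
| --- | --- | --- |
| 1 | Taking part in another trial | No |
| 2 | General or ocular pathology affecting treatment | No; could be read to include them |
| 3 | Allergy or intolerance to cycloplegic drops | No |
| 4 | Strabismus | No |
| 5 | Amblyopia | No |
| 6 | Past ocular injury or surgery | No |
| 7 | Earlier myopia control treatment | No |

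Named in 0 of 7.

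**2. Does the general criterion do the same job?** Not reliably. The risk section asks whether the child should wear the lens; criterion 2 asks whether a pathology could affect the treatment. An investigator could reasonably decide that a balance disorder has no bearing on myopia treatment and enrol the child. The list also names strabismus, amblyopia and ocular injury or surgery separately, although criterion 2 could arguably cover them. The protocol therefore does not rely on criterion 2 for other known conditions of concern.

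**3. Does another pre-randomisation step catch it?** Medical history is recorded at Visit 1, but nothing links it to this contraindication. The functional tests listed there (cover test, Titmus, Worth four dot) are visual.

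**4. Does a later step catch it?** The section on terminating participation covers fast progression or other significant refractive change, and reduced acuity with the trial spectacles. It does not name vestibular disorders. The risk section lets the investigator exclude a child after a report of unexpected events during wear, so that route starts only once the child has been exposed.

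**5. Could both risk items be entry criteria?** No. Discomfort arises only during wear and has to be handled then. A pre-existing vestibular disorder can be known at Visit 1. The gap concerns this item alone.

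**6. Size.** Inputs from the Enrollment section: 136 children, 68 allocated to the test lens.

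Chance that an enrolled child is allocated to the test lens = 68 / 136 = 0.50.

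The documents give neither the frequency of vestibular disorders in this population nor the share that criterion 2 would catch. The expected number of affected children cannot be calculated, and none is assumed.

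**The case against.** The strongest reply is that the protocol already covers the case. The treatment is wearing the lens all day. A general-health condition that rules out wearing it affects the treatment on an ordinary reading, and the risk section shows the investigator how to apply the general criterion. Verification and history-taking both come before randomisation, and no individual condition is itemised under medical history. If a case is missed, the investigator may exclude the child on a report without knowing the arm, stopping a control child carries no lens-related risk, and a contraindicated child is plausibly one of the withdrawal cases in which disclosure is allowed. The 50% is only the allocation ratio, and the number of children wrongly given the test lens could be zero.

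Much of this stands. The sections do not flatly contradict each other, the general criterion can be read to include the condition, and the procedures for stopping wear and withdrawing are not at fault. The size is indeed unknown and may be nil.

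It does not close the gap. The risk section leaves no discretion, whereas the general criterion rests on judgement and concerns the treatment, not danger to the child. The later routes act only after the child has started wear, or at the price of losing a randomised participant or breaking the mask.

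**Conclusion.** The point holds, as a minor one. The protocol names vestibular disorders as a reason not to wear the test lens and does not name them in any of its seven exclusion criteria, so the contraindication depends on how each investigator reads a general criterion.

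Its size can be stated only conditionally: an affected child who is enrolled has an even chance of being given the test lens, to be worn throughout the day in a trial lasting 24 months per child. The conclusion rests on the protocol's wording alone and assumes no prevalence or detection rate. It is worth correcting because the contraindication is the sponsor's own and the correction is simple.

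**What to change.** Add one exclusion criterion that applies to all children before allocation: *Vestibular disorders (known or reported in the Visit 1 medical history)*. Add a matching question to the Visit 1 medical history and check the answer as part of verifying the enrolment criteria.

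The cost is one line in the exclusion list and one question at screening. A very small number of otherwise eligible children may be lost; by the risk section these children should not wear the test lens anyway. The provisions for stopping wear and for withdrawal can stay as they are.

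### Two lens-related exits lead only out of the trial, and nothing keeps a child who stops the spectacles in the scheduled measurements; the loss is probably small and cheap to prevent

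*Protocol*

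**What the plan says.** Three statements in the Protocol bear on a child who does not tolerate the spectacles.

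- **Reported unexpected events** (Risk Evaluation/Adverse Events): "The investigator will decide based on the report whether the child should be excluded from continuing the trial".
- **Reduced acuity** (Terminating the participation in the trial, item 2): "Should the far/near VA with the trial spectacles will be less than the best corrected VA of the patient", then "the investigator will consider recommending the patient to discontinue the participation in the trial". No size of shortfall is set.
- **Not wearing the lens** (Risk Evaluation/Adverse Events): "a child should not wear this lens in case of one/more of the following exist", followed by discomfort that may endanger the child and by vestibular disorders. This concerns wear only and is silent on later visits.

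The same section says that the test design, through its peripheral power, will "induce a certain amount of aberrations in the peripheral areas of the lens". It also calls adverse events unlikely and notes that none had been reported in the parallel trial, in which most children had worn the spectacles for a few months.

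Data Analysis compares the arms at 6, 12, 18 and 24 months, by t-test and by linear mixed models. Unscheduled visits (Trial Plan) are optional and their content is left to the investigator, so they do not provide follow-up after stopping.

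**The concern.** Stopping a treatment and leaving a trial are different events. The Protocol treats them as one for the two exits that are tied most closely to how the lens is tolerated. A child who leaves by either route contributes no later cycloplegic refraction or axial length, and one who leaves before month 6 contributes no post-baseline outcome.

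Whether a child is measured after stopping is fixed by the visit schedule, so it is a protocol matter. A statistical analysis plan can choose how to handle missing values but cannot supply measurements that were never taken.

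At stake is the comparison of the groups as randomised. The test lens has peripheral aberrations and the control is single vision, so intolerance may occur more often in the test arm. A child who stops the test lens may go back to progressing at the control rate. If such children disappear from the data, the test arm looks slightly better than it would with everyone measured.

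**Working it through.** **Inputs** (Sample size calculation and Enrollment): "The annual myopia progression rate (in objective refraction) in children in Israel is estimated as 0.6D"; expected effect 30%, or 0.18 D/year; "Taking into account a standard deviation of the progression rate of 0.35D"; 60 children per group needed, 68 per arm enrolled, about 5% dropout. Power and sidedness are not stated; 80% and two-sided 5% are assumed because they reproduce the stated size. Exit rates are not given, so every rate below is an assumption.

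**1. The plan's own figure.** n per group = 2 × (1.960 + 0.842)² × 0.35² / 0.18² = 59.4, rounded up to 60. Total: 120 × 1.05 + 10 = 136. Both agree with the Protocol.

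**2. Yardstick.** Standard error of the difference with 60 per arm = 0.35 × √(2/60) = 0.0639 D.

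**3. Worst case for the event exit.** Suppose a share q of the test arm leaves before month 6, no control child leaves this way, and the leavers would have progressed at the control rate. If the children who remain show 0.18 D/year, the effect as randomised is 0.18 × (1 − q). The shift is 0.18q and the relative overstatement is 1/(1 − q) − 1.

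| Test-arm exits | Shift (D/year) | Overstatement | Shift / SE |
|---|---|---|---|
| 1 of 68 | 0.0026 | 1.5% | 0.04 |
| 2 of 68 | 0.0053 | 3.0% | 0.08 |
| 5% | 0.0090 | 5.3% | 0.14 |
| 10% | 0.0180 | 11.1% | 0.28 |

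If leavers keep half the benefit, the overstatement is 1/(1 − 0.5q) − 1, which gives 0.7%, 1.5% and 2.6% for the first three rows. The 5% row already puts a share equal to the whole planned dropout rate into one exit in one arm. A harsher case, with 10% of the arm leaving and leavers progressing a full SD faster than stayers, shifts the arm mean by 0.10 × 0.35 = 0.035 D, or 19% of 0.18 D.

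**4. Loss of information.** By normal approximation, power with 68 per arm is 85.1%. It becomes 84.1% if 5% leave one arm and 83.2% if 5% leave both.

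**5. When the acuity exit can be triggered.** The Trial Plan names acuity measured with the trial spectacles at the delivery visit, about 10 days after screening. At the planned control rate, progression by then is 0.60 × 10/365 = 0.016 D. For the 6-monthly visits it lists best corrected far and near acuity and does not mention the trial spectacles. The delivery procedures are repeated only when new lenses are supplied, and the correction is then current. At the checks that the Protocol names, a shortfall would therefore hardly come from progression. No direction or size can be derived for this exit.

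**The case against.** The strongest reply is that the matter is immaterial. Both rules leave the decision to the investigator, neither forbids further follow-up, and data are lost only if a child actually leaves. Adverse events are expected to be unlikely. All of this stands, and it keeps the point small. It does not supply the missing provision: a site that follows the text has no instruction to go on measuring a child who stops.

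A second reply is that the mixed model uses the visits a child did attend. That is correct for later leavers. It does not help with a child who leaves before month 6, and measurements taken on the lens do not show what happens after it is stopped.

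A third is that the target may be the lens as worn. If so, and if leavers are otherwise like stayers, the event exit costs data but causes no bias.

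A reader might also infer that the acuity exit biases the other way by removing fast-progressing control children. The re-lensing rule, "change from last refraction of at least -0.50D, a new lens order should be made for new lenses", makes this tempting, because the planned six-month changes of 0.60/2 = 0.30 D (control) and 0.42/2 = 0.21 D (test) both fall below it. The documents do not support the inference. Acuity with the trial spectacles is named only at delivery, and a later check is possible but not stated. Aberration blur could equally send test children through this exit. A test child one SD above the mean also stays below the threshold, at (0.42 + 0.35)/2 = 0.385 D, and equal losses of such children in both arms would cancel.

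**Conclusion.** The point holds as a gap in the follow-up rules, not as a demonstrated bias. Both exits name only departure from the trial, and no section retains a child who stops the spectacles, so later outcomes are lost for children who leave for lens-related reasons.

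The size is probably small: about 0.009 D/year, roughly 5% of the effect and 0.14 SE, if 5% of the test arm left early and lost all benefit. That figure rests on an assumed exit rate, on exits in the test arm only and on return to the control rate. It would grow if exits were more frequent, and the acuity trigger has no threshold to limit its use.

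The direction for the event exit is an inference from the lens design; for the acuity exit it is not established. The separate exit for progression above 1.00 D after one year is not part of this point. The rating is a cheap improvement worth considering.

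**What to change.** In Risk Evaluation/Adverse Events and in item 2 of Terminating the participation in the trial, add one or two sentences that separate stopping the spectacles from leaving the trial. A child who stops keeps the remaining scheduled cycloplegic refraction and axial-length visits unless consent is withdrawn, and is analysed in the assigned group. Record the stop date, the reason and any other myopia-control treatment started. Decisions on who should stop wearing the lens for safety remain as they are.

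The cost is a protocol amendment with ethics committee approval and continued cycloplegic visits for a few children who have already had difficulties. The 15-minute peripheral refraction measurement need not be continued for them. The estimated effect may come out slightly smaller, because children who lost the benefit would now be counted.
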